## Abstract

**Background:**

Despite the wide use of parenteral nutrition (PN) in neonatal intensive care units (NICU), there is limited evidence regarding the optimal time to commence PN in term and late preterm infants. The recommendations from the recently published ESPGHAN/ESPEN/ESPR/CPEN and NICE guidelines are substantially different in this area, and surveys have reported variations in clinical practice. The aim of this randomised controlled trial (RCT) is to evaluate the benefits and risks of early versus late PN in term and late preterm infants.

**Methods/design:**

This study is a single-centre, non-blinded RCT in the NICU of Perth Children’s Hospital, Western Australia.A total of 60 infants born ≥34 weeks of gestation who have a high likelihood of intolerance to enteral nutrition (EN) for at least 3-5 days will be randomised to early (day 1 or day 2 of admission) or late commencement (day 6 of admission) of PN after informed parental consent. In both groups, EN will be commenced as early as clinically feasible. Primary outcomes are plasma phenylalanine and plasma F_2_-isoprostane levels on Day 4 and Day 8 of admission. Secondary outcomes are total and individual plasma amino acid profiles, plasma and red blood cell fatty acid profiles, in-hospital all-cause mortality, hospital-acquired infections, length of hospital/NICU stay, z scores and changes in z scores at discharge for weight, height and head circumference, time to full EN, duration of respiratory (mechanical, non-invasive) support, duration of inotropic support, the incidence of hyper and hypoglycaemia, incidence of metabolic acidosis, liver function, blood urea nitrogen, and C-reactive protein (CRP).

**Discussion:**

This RCT will examine the effects of early versus late PN in term and late preterm infants by comparing key biochemical and clinical outcomes and has the potential to identify underlying pathways for beneficial or harmful effects related to the timing of commencement of PN in such infants.

**Trial registration:**

ANZCTR; ACTRN12620000324910 (3rd March 2020)

## Background

Term and late preterm infants (≥34 weeks of gestation) may suffer from conditions that predispose them to critical illness needing admission to Neonatal Intensive Care Units (NICU). These include persistent pulmonary hypertension of the newborn (PPHN) [1], meconium aspiration syndrome [2], hypoxic-ischaemic encephalopathy (HIE) [3], sepsis [4], critical congenital heart disease [5], congenital diaphragmatic hernia [6], and other major surgical conditions [7].

During periods of acute illness, the provision of enteral nutrition (EN) may be unachievable, which necessitates the use of parenteral nutrition (PN). PN involves the administration of glucose, amino acids, lipids and various micronutrients and is usually indicated in infants in whom EN is contraindicated or delivers insufficient protein and energy requirements [8].

Despite the wide use of PN in NICU, there is limited evidence regarding the optimal time to commence PN in term and late preterm infants [9, 10]. Evidence regarding early versus late PN in term and late preterm infants is limited to the subgroup analysis of 209 term infants [11] from the PEPaNIC trial, a multi-centre RCT of critically ill children (*N* = 1440; birth to 17 years) [12]. In that study, the early PN group received PN within 24 h of admission and late PN group, after 7 days. They reported that, late PN was associated with earlier discharge from the ICU but increased the risk of hypoglycaemia in neonates [11]. Due to the various study limitations and concerns about hypoglycaemia, experts do not recommend withholding PN for 7 days as standard practice [10, 13]. Furthermore, our Cochrane review, which only identified data from the PEPaNIC trial, also concluded that the quality of the evidence was low, highlighting the need for further RCTs [9].

A recent retrospective cohort study found that preterm infants (born between 30^+ 0^ and 32^+ 6^ weeks’ gestation) who were commenced PN within the first 7 days of life had a higher rate of survival but higher rates of necrotising enterocolitis, bronchopulmonary dysplasia, late-onset sepsis and the need for surgical procedures [14].

The recommendations from the recently published ESPGHAN/ESPEN/ESPR/CPEN and NICE guidelines are substantially different in this area. The NICE guidelines recommend the commencement of PN within 72 h after birth if no progress is made with EN in term and late preterm infants [15]. On the other hand, the ESPGHAN/ESPEN/ESPR/CPEN guidelines recommend clinicians to consider withholding *parenteral amino acids* for 1 week in critically ill term infants; they do not make a recommendation on the timing of *parenteral lipids* [16]. The surveys have reported variations in clinical practice, demonstrating the uncertainties in this area [17–19].

Amino acids are major and essential constituents of PN; they are precursors of protein synthesis and signalling molecules that regulate energy metabolism, cell proliferation and survival [20]. Early parenteral amino acids may have beneficial effects by preventing catabolism, reducing the risk of hyperglycaemia and enhancing the secretion of insulin-like growth factor and may lead to improved growth and neurodevelopmental outcomes [21–27]. However, there are concerns about the harmful effects of parenteral amino acids such as hyperammonaemia, azotaemia, metabolic acidosis, free radical injury, and slower growth of head circumference and metabolic syndromes later in life [24, 28–31].

High levels of plasma phenylalanine and other amino acids have been observed in critically ill term and late preterm infants [32–38], suggesting metabolic derangements of certain amino acids during critical illness. If such infants are administered parenteral amino acids early during their critical illness, plasma levels may reach very high levels, leading to potential harm. In the cohort of critically ill children undergoing cardiac surgery, non-surviving children had higher plasma amino acid levels compared to survivors [39]. In an RCT of extremely low birth weight infants, those receiving early and higher parenteral amino acids had higher plasma amino acid levels [40]. The early and high amino acid group had a lower mental developmental index (MDI) at 18 months and poor overall growth at 18- 24 months [41]. Authors reported that higher levels of phenylalanine, isoleucine, valine, and leucine, were associated with poor growth and low MDI and/or Psychomotor Developmental Index scores [41]. More recently, in the subgroup analysis of 209 term infants of the PEPaNIC trial, higher amino acid doses were associated with prolonged ICU stay and duration of mechanical ventilation [11]. The authors postulated that the harm associated with parenteral amino acids might be caused by the suppression of autophagy, the amino acid load being above the metabolic capacity of the liver and kidney or suboptimal composition of amino acid formulations [11].

Intravenous lipid emulsions are another important component of PN. They provide a concentrated source of energy, essential fatty acids (EFA) and long-chain polyunsaturated fatty acids (LCPUFA). EFA deficiency can be prevented by giving as little as 0.5-1 g/kg/day lipid emulsions [42–44]. Early parenteral lipids can prevent EFA deficiency, increase LCPUFA levels and have the potential to improve neurodevelopmental outcomes. On the other hand, lipid emulsions may cause harmful effects by exacerbating free radical activity [45, 46], increasing the risk of sepsis [47, 48], worsening respiratory function by decreasing arterial oxygenation [49–51], increasing the risk of kernicterus in infants with hyperbilirubinaemia due to free fatty acids displacing bilirubin from albumin binding sites [52] and may worsen pulmonary hypertension [53].

Intake of PUFA from parenteral lipids and various components of PN is associated with the production of free radicals resulting in an increased risk of membrane peroxidation and may worsen the oxidative stress in critically ill infants [31, 54–61]. Basu et al. found high malondialdehyde levels (a marker of free radical activity) in critically ill as well as stable infants receiving PN, but the levels were even higher in critically ill infants [45]. Given that critically ill infants in the NICU (e.g. HIE, PPHN, necrotising enterocolitis, congenital heart disease and sepsis) are already under oxidative stress [62–67], early commencement of PN may worsen it.

Furthermore, evidence is accumulating that aggressive nutrition during the early phase of critical illness may be associated with enhanced oxidative stress and attenuation of autophagy [68]. In mechanically ventilated adults with systemic inflammatory response syndrome, oxidative stress (measured by total plasma F_2_-isoprostanes) was significantly higher in participants in the second or third versus the first tertile of real-time energy flow rate [69]. Hence, the authors of that study postulated that high energy induced oxidative stress may be a potential mechanism of harm associated with early PN use in adults [69].

This RCT will examine the effects of early versus late PN in term and late preterm infants by comparing key biochemical and clinical outcomes and has the potential to identify underlying pathways for beneficial or harmful effects related to the timing of commencement of PN in such infants.

## Methods/design

### Aim and hypothesis

Our current RCT aims to evaluate the benefits and risks of early versus late PN in term and late preterm infants. We hypothesise that late commencement of PN will achieve lower (and more physiological) levels of plasma phenylalanine and plasma F_2_-isoprostanes on Day 4 and Day 8 compared to early commencement of PN in term and late preterm infants.

### Objectives

#### Primary objective

The key objective of this RCT is to compare the effect of early vs late commencement of parenteral nutrition on plasma phenylalanine and F_2_-isoprostane levels on Day 4 and Day 8 in term and late preterm infants.

The *secondary objectives* are to:Characterise the overall plasma amino acid and fatty acid profiles (red blood cell (RBC) and plasma) of infants receiving early versus late PNDescribe the clinical outcomes of early versus late PN in study infantsExplore associations of plasma amino acid and fatty acid profiles (RBC and plasma) and plasma F_2_-isoprostane levels with clinical and other biochemical outcomesPerform cost analysis of early versus late PN from an Australian public hospital perspective

### Study design and setting

A prospective, single-centre, non-blinded RCT in the neonatal intensive care unit (NICU) of Perth Children’s Hospital (PCH), Child and Adolescent Health Service (CAHS), Perth, Australia. PCH-NICU is a 30-bed tertiary referral centre that provides intensive and high dependency care for critically ill neonates. Over 800 infants are admitted to our NICU each year and all infants are out born. The study schedule is shown in Fig. 1.

**Fig. 1 Fig1:**
[figure not shown]
Study Schedule

### Study population

#### Inclusion criteria

Term or late preterm infants born ≥34 weeks of gestation and ≤ 28 days old, admitted to NICU from another hospital who have a high likelihood of being unable to tolerate enteral feeds for at least 3 to 5 days-This definition and judgement was based on our retrospective audit of 124 late preterm and term infants (currently in peer review), which found that conditions such as gastroschisis, tracheoesophageal fistula, meconium aspiration syndrome, PPHN and HIE wereunlikely to tolerate full enteral feeds by five days of admission.Informed parental/guardian consent

#### Exclusion criteria

Infants who received PN at a referring hospitalInfants with a suspected inborn error of metabolismInfants who previously established full enteral feeding or has had more than 50% of total fluids as EN for more than 12 h since birthInfants admitted from home

### Recruitment

A parent/guardian of an eligible infant will be approached by the Coordinating Principal Investigator (CPI) or her delegate and invited to participate in this study. The CPI will accredit the delegates to take parental consents. Informed parental consent to trial participation is required by Day 2 of admission so that the trial intervention and data collection can be initiated by Day 2 of admission.

### Interventions

With Day 1 defined as the day of admission if admitted before 12.00 pm, and the following day if admitted after 12.00 pm, participants will be allocated to one of the two types of interventions, either ‘Early PN’ or ‘Late PN’. Day 1 of admission is not always Day 1 of life as participants will be out born.

#### Early PN (standard care or control group)

Infants randomised to ‘Early PN’ will be commenced PN on Day 1 or Day 2 of admission to the NICU.

#### Late PN (intervention group)

Infants randomised to ‘Late PN’ will commence PN only after the completion of Day 5 of NICU admission. If an infant randomised to ‘late PN’ does not require PN after Day 5, the infant will still be included as being in the ‘Late PN’ group and analysed as such.

#### Justifications for the definition of ‘late PN’ (intervention group)

Early versus late parenteral nutrition (PN) trials in adults and children (birth to 17 years) defined early PN as “within 24 h of admission” and late PN as “after 7 days of admission” [12]. As highlighted by Mehta et al., they are two extreme timings and practised only in a very few units [13]. Hence such a study design is unlikely to be feasible in term and late preterm infants.

We conducted a survey (September 2019) to find the current practice and to seek the opinions of clinicians (neonatologists and paediatric intensivists) in Australia and New Zealand [70]. We found that 43% of respondents (32/74) thought that commencing parenteral amino acids “within 24 h of admission” is beneficial, while 32% (24/74) felt that late commencement “after 72 h” is optimal. None of the respondents felt “after 7 days of admission” was the optimal time to commence parenteral amino acids. Similarly, 41% (31/75) thought that commencement of parenteral lipids “within 24 h of admission” is optimal, whereas 35% (26/74) felt late commencement “after 72 h” to be beneficial. Only one respondent thought “after 7 days of admission” was an optimal time to commence lipids [70].

The Cochrane review (Moon et al), defined late PN as “after 72 h of admission” [9].

After carefully considering the above information, our trial steering committee decided that ‘late PN’ should be > 72 h but < 7 days of admission. We settled on day 6 as the definition for late PN to maximise the time difference between the early and late PN groups, while at the same time ensuring feasibility for future multicentre RCTs.

### PN

PN will be defined as the administration of any amount of intravenous amino acids and/or lipid emulsion. Administration of PN will be either via peripheral intravenous cannula or central venous access device. Prescription of PN (including the type of PN, dosage and rate of administration) will be determined by the treating clinician daily, depending on the infant’s clinical progress and according to the CAHS Neonatology Guidelines (“Nutrition: Volume and Nutritional Requirements” and “Parenteral Nutrition”). Usually, on day 1 of admission, 60 to 80 mL/kg/day of parenteral amino acids solution (2.3% amino acids and 12% glucose) and 6 mL/kg/day of lipid emulsion 17% are administered to infants to provide 1.4-1.8 g/kg/day of amino acids and 1 g/kg/day of lipids respectively. When an infant receives 140 mL/kg/day of parenteral amino acids and 18 mL/kg/day of lipid emulsions, amino acid and lipid intake of 3.2 g/kg/day and 3 g/kg/day are reached, respectively.

All PN formulations will be prepared by the Pharmacy Department at PCH or an external compounding provider. Standard PNs used in the NICU contains 2.3 g or 3 g/100 mL of amino acids and 12 g or 8 g/100 mL of glucose with standard amounts of electrolytes, trace elements and heparin. Lipid emulsions 20% (SMOF®, Fresenius, Uppsala, Sweden) consisting of soya oil (30%), medium-chain triglyceride (30%), refined olive oil (25%) and fish oil (15%) will be used as the source of parenteral lipids. Both fat-soluble (Soluvit N®, Fresenius, Uppsala, Sweden) and water-soluble vitamins (Vitalipid N®, Fresenius, Uppsala, Sweden) will be added to the lipid emulsion in the Pharmacy, resulting in lipid emulsion 17%. Each 6 mL of lipid 17% contains 1 g fat.

Infants randomised to the ‘early PN’ group will receive PN formulation as prescribed by the treating clinician on Day 1 or Day 2 of admission to NICU.

Infants randomised to the ‘late PN’ group will receive glucose and sodium chloride solutions as per infant’s needs up to Day 5 and then commence PN from Day 6 of admission to NICU.

PN will be prescribed and administered according to the CAHS Neonatology Guidelines: Volume and Nutritional Requirements. Administration of PN and glucose, sodium and other electrolytes will be titrated according to routine biochemical results (examples: blood glucose, serum sodium, potassium, magnesium, calcium) by the treating clinician.

### EN

EN will be commenced as early as clinically feasible in both intervention groups per the CAHS Neonatology Guidelines: Enteral feeding- Initiation and progression. When EN provides 80-100% of target nutrition intake (150 mL/kg/day) or clinically appropriate, PN will be stopped by the treating clinician. EN of choice will be mother’s own milk. Standard formula milk will be used if mother’s milk supply is inadequate or if it is mother’s preference. Extensively hydrolysed formulas will be used occasionally only if clinically indicated.

### Assignment of interventions

#### Random sequence generation

Group assignment will be allocated by the Clinical Trial Pharmacist at PCH using a computer-generated randomisation sequence in a 1:1 ratio in block sizes of 2 and 4 and stratified according to the primary diagnostic category (medical or surgical) to minimise selection bias.

#### Allocation concealment

Allocation concealment will be achieved by using opaque sealed envelopes. Once consent is provided, the CPI or delegate will open the next opaque sealed envelope to allocate the infant to the ‘Early PN’ or ‘Late PN’ group.

#### Blinding

Blinding of families, healthcare providers and study investigators to group allocation is not possible for this intervention. However, the laboratory personnel responsible for plasma amino acids, F_2_-isoprostanes and plasma/RBC fatty acids and the trial biostatistician will be blinded to allocations.

### Study outcomes

#### Primary endpoints

The two primary endpoints of this RCT are levels of (a) plasma phenylalanine (μmol/L) and (b) plasma F_2_-isoprostane (pg/mL) on Day 4 and Day 8 of admission.

##### Justifications for plasma phenylalanine as the primary endpoint

We hypothesise that early parenteral amino acids may not be tolerated in critically ill infants in the acute phase of illness and may lead to high plasma phenylalanine concentrations.

There are many reports describing abnormal plasma amino acid profiles (especially phenylalanine) in critically ill neonates [32, 33, 36–38, 71]. High phenylalanine levels have been reported in infants with PPHN, peritonitis, HIE, sepsis and congenital heart defects (post-operative) [32, 33, 36–38, 71]. Suggested mechanisms for such high levels are impaired phenylalanine hydroxylase (PAH) activity due to oxidative stress [36], decreased metabolism in the liver [33], increased muscle breakdown [37], reduced incorporation of phenylalanine into muscle protein [37], altered rate of hepatic conversion of phenylalanine to tyrosine [37]. The relevance of the high phenylalanine levels during critical illness is that it is associated with higher mortality [33, 39], poor growth and neurodevelopmental outcomes in neonates [41]. It is well known that elevated levels in conditions such as phenylketonuria are associated with brain injury [72]. Hence, we have chosen phenylalanine as a primary endpoint and also to evaluate full amino acid profile in our study infants.

##### Justifications for plasma F_2_-isoprostanes as the primary endpoint

Another potential mechanism through which early PN can cause harm is through worsening of oxidative stress. Oxidative stress is a major characteristic of various diseases in humans. In the context of critically ill term and late preterm infants, sources of oxidative stress are birth trauma, reperfusion injury after hypoxia/ischaemia, oxygen therapy, acidosis, phototherapy, mechanical ventilation, infection, and inflammation [73–75]. Oxidative stress is present in conditions that predispose to critical illness in term and late preterm infants. The examples are congenital heart disease [62], PPHN [63], HIE [64], NEC [65] and sepsis [66, 67]. In the presence of oxygen, nutrients such as lipids, amino acids and vitamins become potent electric donors that promote the generation of peroxides [31]. Polyunsaturated fatty acids present in lipid emulsions are susceptible to oxidation [54, 57]. Furthermore, various studies have shown that oxidation of amino acid solutions, vitamins and trace elements can also result in increased oxidative stress [45, 58–61]. Hence, early intake of PN may worsen the oxidative stress in critically ill infants.

It is well known that F_2_-isoprostanes are sensitive markers of oxidative stress. They are prostaglandin like substances that are formed in vivo by free radical-induced peroxidation of arachidonic acids [76]. F_2_-isoprostanes are a. chemically stable, b. specific products of peroxidation, c. formed in vivo, d. present in detectable amounts in all normal tissues and biological fluids and e.unaffected by lipid contents in the diet [77]. All these characteristics make them a suitable candidate as a biomarker of oxidative stress. In addition, recent studies have found that increased F_2_-isoprostane levels are associated with poor neurodevelopment and neurological outcomes in infants [62, 78, 79] Hence, we have chosen plasma F_2_-isoprostanes as one of the primary endpoint in our RCT.

#### Secondary safety endpoints

Incidence of hypoglycaemia [blood glucose < 2.6 mmol/L] (%)Incidence of hypoglycaemia resistant to parenteral glucose administration (%)In-hospital mortality [defined as death from any cause during the hospital stay] (%)Neonatal mortality [defined as death in the first 28 days from birth since birth from any cause] (%)

#### Secondary efficacy endpoints

Total and individual plasma amino acids on Day 4 and Day 8 of admission [Plasma amino acid profiles in healthy term breastfed infants have been studied, describing the optimal plasma amino acid pattern for growth and development [80, 81]. These data will be used as reference values] (μmol/L)Plasma and RBC fatty acid profiles on Day 4 and Day 8 of admission [Plasma and RBC fatty acid compositions of healthy term breastfed infants have been reported [82–86]. These data will be used as reference values] (% total)

#### Secondary clinical endpoints

Duration of NICU stay (days)Duration of hospital stay (days)Duration of respiratory support [defined as mechanical ventilation via endotracheal tube OR non-invasive ventilation (NIPPV) or continuous positive airway pressure (CPAP, or humidified high-flow nasal prong (HFNP) therapy] (days)Duration of mechanical ventilation via an endotracheal tube (days)Weight, length and head circumference z scores at the time of discharge from the hospitalChanges in z scores for weight, length and head circumference from baseline todischargeTime to full EN (days). Full EN will be defined as enteral nutrition intake of ≥150 mL/kg/day.Number of hypoglycaemia episodes [blood glucose < 2.6 mmol/L] (counts)Number of hyperglycaemia episodes [blood glucose> 8.3 mmol/L] (counts)Incidence of hospital-acquired infections [defined as positive growth on blood culture or cerebrospinal fluid or sterile urine or wound swabs drawn 48 h after admission to NICU] (%)Duration of antibiotic treatment (days)Duration of ionotropic support (hours)Highest blood urea nitrogen (BUN) during hospital stay (mmol/L)Incidence of metabolic acidosis [pH < 7.25 or base excess <− 5] during hospital stay (%)Highest C-reactive protein during hospital stay (mg/L)Incidence of liver dysfunction [raised liver function tests including total bilirubin (> 200micromol/L), alkaline phosphatase (> 380 units/L), γ-glutamyltransferase (> 150 units/L), alanine transferase (> 35 units/L)] during hospital stay (%)Incidence of cholestasis [serum level of direct bilirubin> 20% of total serum bilirubin or serum level of direct bilirubin > 34 mmol/L] during hospital stay (%)

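### Peak BUN, peak CRP, metabolic acidosis, liver dysfunction and cholestasis are defined over a window that opens at admission, before randomisation, which dilutes the comparison of the arms

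*Protocol article*

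**What the plan says.** In the protocol article, *Secondary clinical endpoints* lists "Highest blood urea nitrogen (BUN) during hospital stay (mmol/L"), "Highest C-reactive protein during hospital stay (mg/L") and "Incidence of metabolic acidosis [pH < 7.25 or base excess <− 5] during hospital stay". Liver dysfunction and cholestasis carry the same window. None of the five is said to start at randomisation.

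The timing of allocation follows from three other sections.
- *Recruitment*: "Informed parental consent to trial participation is required by Day 2 of admission".
- *Allocation concealment*: the envelope is opened only once consent has been given.
- *Interventions*: "Day 1 defined as the day of admission if admitted before 12.00 pm, and the following day if admitted after 12.00 pm".

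The hypoglycaemia endpoints differ. "Incidence of hypoglycaemia [blood glucose < 2.6 mmol/L"] under *Secondary safety endpoints* and "Number of hypoglycaemia episodes [blood glucose < 2.6 mmol/L] (counts") under *Secondary clinical endpoints* have no stated window at all.

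Under *Statistical analyses* the five endpoints fall into the remaining group of clinical outcomes that is only described. No baseline value is named for them.

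**The concern.** An outcome that is to be compared between randomised arms should be able to respond to the allocation. A window that opens at admission lets in values measured before either strategy has begun. The population makes this plausible: *Inclusion criteria* names "conditions such as gastroschisis, tracheoesophageal fistula, meconium aspiration syndrome, PPHN and HIE" as examples of enrolling conditions, and some of these infants may arrive acidotic or with a raised CRP. A yes/no endpoint met before allocation stays met whatever happens afterwards, and a peak reached before allocation hides any lower peak that follows.

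What is at stake is the reading of safety. The *Background* names azotaemia and metabolic acidosis among the feared harms of parenteral amino acids. BUN and acidosis are the endpoints that would show them, and a diluted contrast could be reported as no difference when one exists.

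**Working it through.** The protocol gives no event rate, standard deviation or power figure for these endpoints, so there is no stated figure to reproduce. The check has three parts.

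**1. How much stay can precede allocation.** Inputs: consent by Day 2 (*Recruitment*), the noon rule (*Interventions*), allocation after consent (*Allocation concealment*). Assumptions: a study day ends at midnight, consent may come at the end of Day 2, and the stay is the one at the trial hospital.
- Admitted just after noon: 12 h to midnight + 24 h (Day 1) + 24 h (Day 2) = about 60 h.
- Admitted just before noon: 12 h (rest of Day 1) + 24 h (Day 2) = about 36 h.

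These are upper limits. An infant whose parents consent soon after arrival has a much shorter interval.

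**2. Yes/no endpoints (acidosis, liver dysfunction, cholestasis).** Let p be the share already positive at allocation, the same in both arms in expectation, and r the risk after allocation, taken as unrelated to earlier status. Then

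observed risk = p + (1 − p) × r, and observed risk difference = (1 − p) × (r₁ − r₂).

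With assumed r of 40% and 20%, a true difference of 20 points and a risk ratio of 2.0:

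| p | Arm 1 | Arm 2 | Difference | Risk ratio |
|---|---|---|---|---|
| 30% | 58% | 44% | 14 points | 1.32 |
| 50% | 70% | 60% | 10 points | 1.17 |
| 70% | 82% | 76% | 6 points | 1.08 |

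The factor 1 − p is exact under the stated assumptions. The values of p and r are illustrative, and the documents supply neither.

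**3. Peak endpoints (BUN, CRP).** The recorded value is the larger of the peak before and the peak after allocation. In a simulation with 30 infants per arm, independent normal peaks and an assumed true shift of 0.7 SD after allocation:
- no values before allocation: difference 0.70 SD, power 77%;
- peaks before allocation with the same mean as the lower arm: difference 0.42 SD, power 49%;
- peaks before allocation with a mean 1 SD higher: difference 0.23 SD, power 18%.

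With a correlation of 0.5 between the two peaks, the last two cases give 0.44 SD (power 45%) and 0.18 SD (power 11%). The direction is the same throughout; the size depends wholly on the assumptions.

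**The far end of the window.** The stay ends at discharge or death, and its length is itself an endpoint. If PN timing changes the stay, time at risk differs by arm. At an assumed constant daily risk of 3%, a 14-day stay gives 1 − 0.97¹⁴ = 35% and a 21-day stay 1 − 0.97²¹ = 47% with no effect on daily risk. Unlike the early values, this could move the contrast in either direction.

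**The case against.** The strongest reply is that outcome collection may in practice begin after consent. *Recruitment* ties the consent deadline to starting the intervention and data collection by Day 2, and the daily collection of clinical data is described under the heading *Data collection following recruitment*. This suggests a later start but does not establish one. Clinical data come from medical records, which also hold the earlier results, and the endpoint wording says otherwise. The wording should therefore be settled.

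Other replies stand and limit the point.
- A reader might infer that early values bias the trial or conceal a harm. They do not favour an arm: under randomisation stratified by medical or surgical category they are balanced in expectation.
- A reader might extend the criticism to hypoglycaemia. There no window is stated, and a condensed article may leave it to the full protocol. Nothing says that values before allocation count. An episode count is also not saturated by one early event.
- The case is weakest for BUN. The documents give no reason to expect its peak before allocation.
- A reader might want the main window closed at Day 8. That would give the late arm at most three days on PN (Days 6 to 8) against about a week in the early arm, and could miss late-arm azotaemia or acidosis. Comparing whole-stay peaks under two strategies is a legitimate contrast.
- The *Discussion* says that the trial is not powered for clinical outcomes. Even so, the protocol applies the 0.05 threshold to all endpoints, so a diluted result may still be read as a test.

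**Conclusion.** The point holds for the five endpoints with an explicit whole-stay window. As written, values from before allocation can set the peak or satisfy the event. The consequence is dilution and added noise, strongest where abnormal values at presentation are common (plausibly acidosis and CRP) and probably small for BUN. The documents do not allow the amount to be computed; the figures above show only how it grows with p.

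These are secondary endpoints. The primary phenylalanine and F₂-isoprostane analyses are fixed at Days 4 and 8 with baseline adjustment and are untouched. Nor do the documents support reading this as a flaw in the stopping comparison, which uses mortality and resistant hypoglycaemia, none of the five endpoints at issue.

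**What to change.** In *Secondary clinical endpoints*, state that highest BUN, highest CRP, metabolic acidosis, liver dysfunction and cholestasis count only samples drawn after randomisation. Report the last value before randomisation as baseline; an abnormality already present can persist past allocation, and the baseline lets the reader see this. Apply the same start to the hypoglycaemia endpoints for consistency.

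Keep the whole-stay values as a descriptive extra. Because the stay may differ by arm, a summary to a common follow-up end could be added as a supplement, but Day 8 should not be imposed as the main window.

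The cost is small but not nil. No new sampling is needed: clinical data are collected daily from the records, and the change requires only the time of randomisation and the times of routine results, assumed to be in those records. Slightly fewer events will be counted. *Trial status* reports 54 infants recruited and both interim safety reviews done, and deviations need prior ethics approval. The change should therefore be approved, dated and fixed before any comparison of these endpoints by arm.
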